## Abstract

•Exercise capacity in patients with CHD is lower than in the general population.•Non-invasive relaxation therapy may be effective in patients with dyspnoea.•Evidence based-medicine on relaxation therapy in the CHD population is poor.•This trial will assess the impact of Sophrology on exercise capacity in CHD patients.

Exercise capacity in patients with CHD is lower than in the general population.

Non-invasive relaxation therapy may be effective in patients with dyspnoea.

Evidence based-medicine on relaxation therapy in the CHD population is poor.

This trial will assess the impact of Sophrology on exercise capacity in CHD patients.

## Introduction

1

Recent advances in the field of congenital heart disease (CHD) have significantly improved the overall prognosis, and currently most children with a CHD will reach adulthood [1]. As a result, after focusing on the survival of this population, more attention is being given to health-related quality of life (HRQoL) and promotion of physical activity [2], [3]. Indeed, cardiopulmonary fitness, as measured by the maximum oxygen uptake (VO2_max_), correlates with HRQoL of children and adults with CHD [4], [5].

We showed that the exercise capacity in children with CHD was moderately but significantly impaired, with a mean overall VO2_max_ decline of 2% per year [6]. Indeed, from a large cohort of nearly 800 patients, we found that children with CHD were three times more affected by physical deconditioning than healthy children [6]. Moreover, we recently reported the existence of an impaired pulmonary function in CHD children, even in the absence of cardiothoracic surgery, impacting cardiopulmonary fitness and HRQoL [7]. In the adult CHD population, abnormal pulmonary function is an independent predictor of prognosis [8].

Exercise-induced dyspnea in patients with CHD may be related to heart failure [9], impaired pulmonary function [6], [10], or muscular deconditioning. Those mechanisms usually interact together and may be aggravated by behavioural and psychogenic obstacles to physical exercise, as the level of anxiety in children and adolescents with CHD [11], as well as in their parents [12], is classically higher than in the general population. As a result, many teenagers and young adults with CHD suffer from an unpleasant feeling of exercise-induced dyspnoea, and cumulated with social and family barriers to physical activity, often “remain on the side-line” at school or in their social life [2], [13], [14]. The current guidelines have reinforced the promotion of physical activity in this population [3], [15], as CHD patients who have been physically active since childhood are less likely to become sedentary adults [14]. When physical deconditioning is diagnosed and managed at an early stage in chronic diseases, participation in rehabilitation and education interventions stand as a chance of reducing cardiovascular morbidity and mortality [16]. Nevertheless, the motivation of teenagers and young adults with CHD to participate in structured hospital-based prevention programs remains limited, such as in transition or rehabilitation programs [17], [18].

In such patients, Caycedian Sophrology may be of interest, as this non-invasive relaxation therapy may focus on exercise-induced dyspnoea. Indeed, we recently reported from a controlled randomised trial, that children and adolescents with asthma were significantly improved in terms of lung function, after only one session of Sophrology [19]. From ancient Greek “σωζ” (harmony), “φρɳν” (mind), and “λ○γία (study), Sophrology is the “study of the consciousness in harmony”, and focuses on breathing, e.g. the only automatic vital function that can become conscious at any time. In the 1960’s, [name], a Colombian neuro-psychiatrist, described this relaxation therapy as a healthcare philosophy, based on the study of human consciousness and the relation between body and mind. Caycedian Sophrology requires a structured method consisting in very practical physical and mental exercises, using techniques such as concentration, deep breathing, relaxation, visualization, and simple movements. Sophrology has been increasingly used in healthcare as an adjuvant therapy to treat pain and/or anxiety in oncology [20], [21], geriatrics [22], obstetrics [23], [24], and dentistry [25].

To our knowledge, Sophrology has not been investigated in the CHD population. From a general perspective, the impact of adjuvant therapies in the CHD population has not been evaluated with a high level of evidence, despite some positive experience reporting the use of clinical hypnosis in children undergoing transesophageal echocardiography [26]. Yet, non-invasive relaxation therapy may be effective on exercise capacity in patients with congestive heart failure [27]. Although acclaimed by the contemporary population, the level of evidence for such adjuvant therapies remains limited. Therefore, the SOPHROCARE randomised controlled trial aims to assess the impact of Caycedian Sophrology on exercise capacity in teenagers and young adults with CHD. We also intend to evaluate, in this population, the impact of Sophrology on patient related outcomes, such as HRQoL and anxiety.

## Methods

2

### Study design

2.1

The SOPHROCARE trial is a prospective, multicentre, randomised, controlled, parallel arm study, with a 12-month follow-up. Participants will be randomly allocated in a 1:1 ratio to either intervention or control group arms, with minimization on centre of inclusion and age groups (13–17 years old vs 18–25 years old). Randomisation numbers will be computer generated and assigned in strict sequence, using a secure, web-based randomisation system (CS RANDOM module, Clinsight Software). Randomisation will be managed by the Clinical Research Unit of Montpellier University Hospital, France, independently from the investigators. All screened subjects will be identifiable throughout the study by a unique subject number.

Eligible patients will be randomised into 2 groups (Fig. 1):•Group 1: intervention group, e.g., patients participating in the Sophrology program in addition to their usual clinical follow-up.•Group 2: control group, e.g., patients will have a regular non-modified clinical follow-up with no Sophrology intervention during the 12-month study period. However, they will be able to participate in the Sophrology program if they wish, once the 12-month study period is over.

**Fig. 1 f0005:**
[figure not shown]

### Setting

2.2

Overall, 5 CHD centres in France will participate in the study (Montpellier University Hospital, Palavas Saint-Pierre Institute, Toulouse University Hospital, Paris Necker Sick Children University Hospital, Bordeaux University Hospital). Patients will be recruited in tertiary care public institutions, and university centres labelled by health authorities as referral centres for complex congenital heart diseases (M3C national health network). The study will be led by a local principal investigator (supported, when necessary, by a co-investigator), a research nurse or fellow, two sophrologists, and a clinical research assistant, all of whom are trained in Good Clinical Practice and in the requirements of the study protocol. Each site will be responsible for the recruitment and scheduled follow-up visits of participants.

### Study population

2.4

Patients with a CHD, as defined by the international ACC-CHD classification [28] and aged from 13 to 25 years old, will be prospectively and consecutively recruited in the participating centres, during an outpatient visit. Patients with a recent (<3 months) medical check-up including a cardiology consultation, an ECG, an echocardiography, and a cardio-pulmonary exercise test (CPET), as detailed in the current European guidelines [29], will be screened (see Table 1).

**Table 1 t0005:** Trial entry.

Inclusion criteria
• Male or female aged 13–25 years old
• Patients with a congenital heart disease (CHD), as defined by the international ACC-CHD classification
• Written informed consent for adult patients, or legal guardians for minors

Exclusion criteria
• Absolute contraindication for cardio pulmonary exercise test
• Cardiac surgery or cardiac catheterization planned during the 12-month study period
• Pregnancy in female patients
• Patient undergoing cardiac rehabilitation during the 12-month study period
• Severe intellectual disability with inability to understand the study procedures and/or the quality of life questionnaire
• Expected difficulty to fully participate to the Sophrology program
• Participation in an interventional research during the 12-month study period

### Intervention

2.5

The SOPHROCARE trial includes a Sophrology program divided into 8 group sessions of 1 h each. All participating centres will use the same program, under the supervision of one of three trained sophrologists ([name]), as in our previous similar study [19]. Each group session will be delivered in-person by one of the sophrologists and involve 5 ± 2 patients.

The first part of the session, lasting about 15 min, will start with a discussion (“pre-sophronic dialogue”), in order to create a climate of confidence, including a brief presentation of sophrology. Patients will be asked about their desires, interests and activities. Then the main part of the session, of approximately 30 min, will lead the patient to a level between awakening and sleep (“sophroliminal level”), using a slow and monotone-directed speech. Patients’ state of relaxation should facilitate “letting go,” focusing on body sensations, and improving their well-being (“sophronisation of vital base”). The techniques will be adapted to patients’ age, availability, and energy. The session will end with a final discussion (“post-sophronic dialogue”), putting into words the different sensations felt without any judgment or interpretation (“pheno-description”).

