### Sample size

2.6

A total of 188 patients need to be recruited (94 intervention: 94 control). The primary outcome is the change in percent predicted maximum oxygen uptake (VO2_max_) between baseline (M0) and 12-month follow-up (M12). The mean VO2_max_ from our own cohort of young patients with CHD is 39.4 ± 8.9 ml/kg/min [6]. In the meta-analysis from Gomes-Neto et al., cardiac rehabilitation increases the VO2_max_ by an average of 13% in young CHD patients [30]. In the SOPHROCARE trial, we hypothesized to observe a VO2_max_ increase of 10% in the Sophrology group. Therefore, with an expected difference of 10%, an 80% power, a bilateral alpha risk of 5%, and potentially 20% of loss to follow-up and/or missing data on the primary outcome, we need to include 78 patients in each group. When considering 20% of loss to follow-up and/or missing data on the primary outcome, we need to include 94 patients in the group 1 and 94 patients in the group 2.

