### Statistical analysis

2.9

A comparative analysis of the baseline characteristics of randomised subjects between the two arms in the study will be performed by giving the frequencies of the different categories for the qualitative variables, and the mean with standard deviation for quantitative variables. Our main analysis will be an intention-to-treat analysis, in which each randomised subject will be analysed in his/her treatment arm. The evolution of the percent predicted VO2_max_ between inclusion (V0) and visit at 12 months (V1) will be compared between the groups using a Student test.

A secondary per-protocol analysis, including all randomised subjects with a valid primary efficacy measurement and with no important protocol deviation (patients who have successfully completed the Sophrology program, with at least 80% of the sessions), will also be carried out to study mechanisms of action. In case of non-comparability of the groups on one of the baseline characteristics, an adjustment will be considered. Analyses will be performed using SAS statistical software (version 9.4; SAS Inc, Cary, North Carolina) using a 5% bilateral alpha risk.

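### Sophrology is given in small groups in one arm only, but neither the sample size nor the Student test allows for correlation within session group or sophrologist

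*Protocol article*

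**What the plan says.** Randomisation is by individual patient: "Participants will be randomly allocated in a 1:1 ratio to either intervention or control group arms", with minimisation on centre and age group (Study design). The intervention is "a Sophrology program divided into 8 group sessions of 1 h each", run "under the supervision of one of three trained sophrologists", and the Intervention section adds: "Each group session will be delivered in-person by one of the sophrologists and involve 5 ± 2 patients". For the control arm, "patients will have a regular non-modified clinical follow-up with no Sophrology intervention during the 12-month study period".

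The Sample size section states: "A total of 188 patients need to be recruited (94 intervention: 94 control". It works from a mean of 39.4 and SD of 8.9 ml/kg/min, a 10% difference, 80% power and a two-sided 5% level. This gives 78 per arm, raised to 94 for losses. It mentions no ICC or design effect.

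In the Statistical analysis section, the change in percent predicted VO2max "will be compared between the groups using a Student test". The only adjustment foreseen is for baseline imbalance.

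**The concern.** This is an individually randomised trial with group treatment in one arm. Intervention patients share a session leader, a discussion before and after each relaxation exercise, and techniques that the plan adapts to the participants. Results may therefore be more alike within a group, or under one sophrologist, than between groups. Controls have no such structure.

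A two-sample Student test treats every patient as independent. If intervention outcomes are positively correlated, the arm mean carries less information than the test assumes. The confidence interval is then too narrow, and a correctly sized test has less power than planned.

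This is not a detail left to an unseen analysis plan, because the article states both the test and the sample size. A later plan could change the model but could not restore power that the sample size never contained.

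**Working it through.** **Inputs from the article.** SD 8.9; difference 10% of 39.4 = 3.94, apparently rounded to 4.0; two-sided 5%; 80% power; 78 per arm before losses; group size 5 ± 2, so 3 to 7; three sophrologists.

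**Assumed.** ICC 0.02, 0.05 and 0.10 (the article gives none); the same total SD in both arms; stable groups with *m* analysed members each; normal approximation.

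**The plan's own figure.** n per arm = 2 × (SD × (1.960 + 0.842) / difference)². With a difference of 4.0 this is 2 × 38.86 = 77.7, so 78; power at 78 is 80.1%. (With 3.94 it is 80.1, so 81.) Then 78 × 1.2 = 93.6, so 94. The stated figure is reached under plain independence and contains no allowance for clustering.

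**Clustering in one arm.**
- Design effect in the intervention arm: DE = 1 + (m − 1) × ICC.
- True SE / naive SE = √((1 + DE)/2).
- Type I error of the naive test = 2 × (1 − Φ(1.96 / that ratio)).
- True SE = 8.9 × √((1 + DE)/78); power = Φ(4.0 / true SE − 1.96).
- Evaluable n per arm for 80% power = (1 + DE) × 38.86, rounded up.

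**One row in full (m = 5, ICC 0.05).** DE = 1 + 4 × 0.05 = 1.20. Ratio = √(2.20/2) = 1.049. Type I error = 2 × (1 − Φ(1.869)) = 6.2%. True SE = 8.9 × √(2.20/78) = 1.495, so power = Φ(2.676 − 1.960) = 76.3%. Evaluable n = 2.20 × 38.86 = 85.5, so 86.

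| m | ICC | DE | SE ratio | Type I error | Power at 78 | n per arm for 80% |
|---|---|---|---|---|---|---|
| 3 | 0.02 | 1.04 | 1.010 | 5.2% | 79.4% | 80 |
| 5 | 0.02 | 1.08 | 1.020 | 5.5% | 78.6% | 81 |
| 5 | 0.05 | 1.20 | 1.049 | 6.2% | 76.3% | 86 |
| 5 | 0.10 | 1.40 | 1.095 | 7.4% | 72.6% | 94 |
| 7 | 0.10 | 1.60 | 1.140 | 8.6% | 69.2% | 102 |

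The type I column applies only if group effects vary around a mean of zero. The power column is for a test that uses the true SE. It excludes the small further cost of estimating the group variance.

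**Sophrologist level.** An equal split, which is assumed, gives 78/3 = 26 patients each. At ICC 0.01, 0.02 and 0.05 the same formulas give DE 1.25, 1.50 and 2.25, type I error 6.5%, 8.0% and 12.4%, and power 75.4%, 70.9% and 59.6%. With three clusters these figures are only indicative, but they show that even a small sophrologist effect could matter more than the group effect.

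**The case against.** A reader might infer that the standard error is certainly too small and the type I error certainly above 5%. The documents do not support that, for five reasons.

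- **No ICC is given.** Every size above is assumed. At 0.02 with groups of 5 the standard error changes by only 2%.
- **The null matters.** Patients are randomised individually. If Sophrology affects nobody, group membership adds no treatment-induced correlation and the Student test keeps about 5%. Inflation needs effects that differ by group or sophrologist and average zero.
- **There is an opposing error.** Allocation is minimised on centre and age group, but the Student test ignores both, which makes its standard error too large. With groups of 5, these factors would cancel an ICC of 0.02 if they explained about 4% of outcome variance (1 − 1/1.04), or an ICC of 0.05 at about 9% (1 − 1/1.10). Those shares are unknown, so the net direction is not established.
- **Closed groups are not stated.** The article gives the size of each session, not whether the same patients stay together for all eight.
- **Losses thin the groups.** With 20% random loss from groups of 5, DE is about 1 + 3.2 × ICC, and the type I errors become about 5.4%, 5.9% and 6.9%.

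All five stand as limits on certainty and size. None makes the Student test right. An opposing error of unknown size does not validate it, and changing membership would complicate the correlation without creating independence. If the effect is real but uneven across groups, the interval is still too narrow.

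**Conclusion.** The point holds in conditional form. The plan has group delivery in one arm, and its sample size and primary test both assume independence. If correlation within session group or sophrologist is positive, the group structure makes the standard error too small and brings power below 80%.

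With 78 evaluable per arm, groups of 5 and an ICC of 0.02 to 0.10, clustering alone costs about 1.5 to 7.5 percentage points of power (80.1% to 78.6% and 72.6%). With groups of 7 and an ICC of 0.10, power is 69.2%. The figures rest on an assumed ICC, stable groups and the plan's own SD and difference. They leave out other questions about the sample size, such as how the 20% loss was added.

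This should be fixed, because it concerns the primary analysis and the remedy is cheap. Confidence is moderate: at the lower ICC values the effect is small, and the net bias of the Student test is not known.

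**What to change.** 1. Record session group and sophrologist for each intervention patient. The case report form is not shown, so this may already be done. The per-protocol rule on 80% of sessions already requires attendance data.
2. Replace the Student test with a partially nested mixed model of the change in percent predicted VO2max. Use a random intercept for session group in the intervention arm only, controls as singletons, arm-specific residual variances, and Satterthwaite or Kenward-Roger degrees of freedom. The planned SAS 9.4 can fit this.
3. Include the minimisation factors, centre and age group, as fixed effects. This also removes the opposing error in the unadjusted test.
4. Examine sophrologist in a sensitivity analysis, because three levels are too few to estimate a variance well.
5. Define the cluster in advance. If membership changes between sessions, use the group that the patient mainly attended.
6. Restate power over an assumed ICC range, with enrolment unchanged.

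The cost is one or two data fields, a changed model, a slightly wider confidence interval and a less favourable stated power.

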### Sample size

2.6

A total of 188 patients need to be recruited (94 intervention: 94 control). The primary outcome is the change in percent predicted maximum oxygen uptake (VO2_max_) between baseline (M0) and 12-month follow-up (M12). The mean VO2_max_ from our own cohort of young patients with CHD is 39.4 ± 8.9 ml/kg/min [6]. In the meta-analysis from Gomes-Neto et al., cardiac rehabilitation increases the VO2_max_ by an average of 13% in young CHD patients [30]. In the SOPHROCARE trial, we hypothesized to observe a VO2_max_ increase of 10% in the Sophrology group. Therefore, with an expected difference of 10%, an 80% power, a bilateral alpha risk of 5%, and potentially 20% of loss to follow-up and/or missing data on the primary outcome, we need to include 78 patients in each group. When considering 20% of loss to follow-up and/or missing data on the primary outcome, we need to include 94 patients in the group 1 and 94 patients in the group 2.

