### Primary outcome

2.7

The main outcome is the change in percent predicted VO2_max_ measured during CPET, between baseline (M0) and 12-month follow-up (M12) (see Table 2).

**Table 2 t0010:** Outcome measures.

Primary outcome
• Maximum oxygen uptake (VO2_max_)

Secondary outcomes
• Quality of life score: PedsQL self-questionnaire (version 13–18 years for adolescents and version 18–25 years for young adults)
• Proxy version of the PedsQL for parents of adolescents (aged 13–18 years old)
• Level of anxiety (STAI self-questionnaire for young adults and the STAI-Children self-questionnaire for adolescents)
• Level of depression (BDI self-questionnaire for young adults and CDI self-questionnaire for adolescents)
• Other cardiopulmonary exercise tests parameters o Ventilatory anaerobic threshold (VAT) o Ventilatory efficiency (VE/VCO2 slope) o Oxygen uptake efficiency slope (OUES) o Oxygen pulse o Respiratory response to hypercapnia using the rebreathing technique with inhaled CO2 and measuring P0.1 at rest
• Clinical outcomes: NYHA functional class, blood pressure, healthcare usage (primary and secondary care contacts, hospitalisation), and medication
• The socio-economic status of the patient and/or the family (only at baseline)
• Safety outcomes
• Acceptability of the intervention to participants

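### The sample size rests on the cross-sectional SD of raw VO2max, not on the SD of the 12-month change in percent predicted VO2max, so the 80% power is not shown to belong to the primary test

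*Protocol article*

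**What the plan says.** Protocol article, section 2.7 (Primary outcome): "The main outcome is the change in percent predicted VO2_max_ measured during CPET, between baseline (M0) and 12-month follow-up (M12"). Section 2.6 (Sample size) names the same endpoint. Section 2.9 (Statistical analysis) says that the evolution of percent predicted VO2max "will be compared between the groups using a Student test". Section 2.7 also explains that percent predicted is obtained by dividing by reference values, so it is a different scale from ml/kg/min.

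The inputs to the calculation, all in section 2.6, are:

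- Mean and SD: "The mean VO2_max_ from our own cohort of young patients with CHD is 39.4 ± 8.9 ml/kg/min".
- Effect: "we hypothesized to observe a VO2_max_ increase of 10% in the Sophrology group".
- Error rates: "with an expected difference of 10%, an 80% power, a bilateral alpha risk of 5" per cent.
- Result: "we need to include 78 patients in each group", then 94 per group (188 in total) for 20% loss.

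The article gives no SD of the 12-month change, no correlation between the M0 and M12 values, and no mean or SD in percent predicted.

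**The concern.** The variable that was sized and the variable that will be tested differ in two respects.

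1. **Unit.** The SD is in ml/kg/min. The endpoint is in percentage points of predicted VO2max.
2. **Type of variance.** The 8.9 describes how patients differ from each other at one time. The Student test uses the SD of M12 minus M0 within patients. The two coincide only at one particular M0-M12 correlation, which the article does not state.

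A third matter follows from the unit. For an endpoint already expressed in percent, a 10% difference can mean a relative 10% or 10 percentage points. These are the same only if the mean is 100% of predicted.

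At stake is the justification for enrolling 188 patients. The 80% tells the reader how likely the trial is to detect its target. If that figure belongs to a different variable, the chance for the planned comparison is unknown.

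**Working it through.** **Step 1. Reproduce the stated number.** Inputs from section 2.6: SD 8.9, two-sided alpha 5% (z = 1.960), power 80% (z = 0.842), 1:1 allocation.

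n per arm = 2 × [SD × (1.960 + 0.842) / difference]²

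- Difference 4 (10% of 39.4 = 3.94, rounded): n = 77.7, so 78. This matches.
- Difference 3.94, unrounded: n = 80.1, so 81. This does not match exactly.
- One-sided testing (64) and 90% power (108), both with 3.94, do not fit.
- 78 × 1.20 = 93.6, so 94. This matches.

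The article does not say outright that 8.9 entered the formula. It is the only SD given, and it returns the stated figure.

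**Step 2. Replace the single-time SD by the SD of change, still on the raw scale.** Assumption: SD 8.9 at both visits, with M0-M12 correlation rho.

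SD of change = 8.9 × √[2(1 − rho)]

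This equals 8.9 only when 2(1 − rho) = 1, that is, rho = 0.5.

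Power of the two-sample t-test with 78 per arm and a difference of 4 (noncentral t), and the n per arm needed for 80% power from the formula in Step 1:

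| rho (assumed) | SD of change | Power at 78 per arm | n per arm for 80% |
|---|---|---|---|
| 0.3 | 10.53 | 65% | 109 |
| 0.4 | 9.75 | 72% | 94 |
| 0.5 | 8.90 | 80% | 78 |
| 0.6 | 7.96 | 88% | 63 |
| 0.7 | 6.89 | 95% | 47 |
| 0.8 | 5.63 | 99% | 32 |

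The table uses 78 and 4, the plan's own figures, so that only the change of variance moves the result. How the 20% loss is added is a separate matter. With 94 × 0.8 = 75 evaluable per arm and a difference of 3.94, power at rho 0.5 would be 76.8% instead of 79.7%. That gap has nothing to do with the SD.

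**Step 3. The endpoint's own scale.** Power cannot be computed here, because the article gives neither the SD of change nor the mean in percent predicted. Purely as an illustration, with assumed SDs of change:

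| SD of change, points (assumed) | n per arm, 10-point difference | n per arm, 8-point difference |
|---|---|---|
| 15 | 36 | 56 |
| 18 | 51 | 80 |
| 20 | 63 | 99 |
| 25 | 99 | 154 |

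Eight points would be a relative 10% if the mean were 80% of predicted, which is also an assumption. For a 10-point difference, 78 per arm gives 80% power only if the SD of change is about 22.3 points.

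**The case against.** **A single-time SD is a common and often cautious choice.** It overstates the SD of change whenever rho exceeds 0.5. Section 2.7 describes one harmonised ergometer protocol and central calculation of all exercise-test variables by one investigator, which favours repeatability. This stands as far as it goes: the trial may have more than 80% power. But no correlation is given, and good measurement does not fix how patients' fitness moves over 12 months.

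**A relative effect does not depend on the unit.** It depends on the coefficient of variation, 8.9/39.4 = 0.226. If percent predicted had the same relative spread, the unit alone would not change N. That is fair, but the equality is an assumption, and it does not deal with the change score. The 10% does read most naturally as relative, since it stands beside a 13% average gain after rehabilitation and reproduces 78 as about 4 ml/kg/min. The article should still say so.

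**The article condenses a fuller protocol.** An SD of change may appear there. The point, however, is not an omission. The article presents a calculation, and the inputs that reproduce it describe a different variable from the endpoint named in the same paragraph.

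**The control arm.** A reader might infer that the calculation also fails because a rise within the Sophrology arm is used as the between-arm difference, while the Introduction reports impaired capacity in children with CHD "with a mean overall VO2_max_ decline of 2% per year". The documents do not support making this a defect. Section 2.6 states an expected difference of 10%. If only controls fell by 2%, the difference would be about 12% of 39.4 = 4.73 ml/kg/min. With SD 8.9 and 78 per arm, 4.73 / (8.9 × √(2/78)) = 3.32, and 3.32 − 1.96 = 1.36, so power is about 91%. Assuming no change in controls is then the cautious choice.

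**Conclusion.** The point holds as a mismatch between the sized variable and the tested one. The stated 80% is the power for a difference of 4 ml/kg/min with a single-time SD of 8.9. It becomes the power for a change score on that scale only if rho is about 0.5. Over assumed correlations from 0.3 to 0.8, power runs from about 65% to 99%. These figures assume equal SDs at both visits and remain on the raw scale, so they show how sensitive the claim is, not what the primary test's power will be.

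Two stronger readings should be resisted. A reader might infer that the trial is underpowered. The document gives no basis for that, because the direction of the error is unknown. A reader might also infer that a null result could not be interpreted. It could, from the confidence interval of the observed difference, which uses the trial's own SD. The type I error and the planned Student test are unaffected. What is wrong is the power claim as written.

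**What to change.** Keep the total at 188 and rewrite section 2.6 on the endpoint's own scale. State:

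- the between-arm difference in mean 12-month change, in percentage points of predicted VO2max, and whether the 10% is relative or in points;
- the SD of the 12-month change in percent predicted VO2max, taken from the sponsor's own exercise-test data if repeat tests are available, or otherwise a single-time SD in percent predicted with a stated correlation and a range around it;
- the resulting power for that difference, or the difference detectable with 80% power, at the number of patients expected to be evaluable.

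This costs a recalculation and one paragraph. It needs no extra patients and no change to the endpoint or test. The downside is that the restated power may be less favourable than 80%, and the sponsor would then have to report it as such.

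### The same 20% loss allowance is attached to both 78 and 94 per group, and 94 comes from multiplying 78 by 1.2 rather than dividing by 0.8, so 188 patients protect 78 evaluable per arm only up to about 17% loss

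*Protocol article*

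**What the plan says.** Section 2.6 of the protocol article opens with the target of 188 patients, 94 per arm, and then justifies it. The inputs are:

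- a cohort mean and SD: "our own cohort of young patients with CHD is 39.4 ± 8.9 ml/kg/min";
- the assumed effect: "we hypothesized to observe a VO2_max_ increase of 10% in the Sophrology group";
- the error rates: "with an expected difference of 10%, an 80% power" and "a bilateral alpha risk of 5"%.

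The sentence that carries the error rates ends: "and potentially 20% of loss to follow-up and/or missing data on the primary outcome, we need to include 78 patients in each group". The next sentence invokes the same loss again and reaches a larger number: "When considering 20% of loss to follow-up and/or missing data on the primary outcome, we need to include 94 patients in the group 1", and likewise for group 2. Section 2.1 (Study design) has patients "randomly allocated in a 1:1 ratio to either intervention or control group arms". Section 2.9 (Statistical analysis) compares the change in percent predicted VO2max between groups with a Student test.

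**The concern.** There are two separate faults in two consecutive sentences.

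First, a loss allowance turns the number needed for analysis into the number to enrol. It can belong to 78 or to 94, but not to both.

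Second, the step from 78 to 94 adds 20% of the analysable number. The loss is a fraction of the patients enrolled, so the analysable number has to be divided by the fraction retained. Adding 20% falls short.

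What is at stake is the consistency of the headline number. The 80% power, the 20% loss and the 188 patients cannot all hold together with a requirement of 78 evaluable per arm.

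**Working it through.** **Inputs.** From section 2.6: two-sided alpha 5%, power 80%, mean 39.4 and SD 8.9 ml/kg/min, effect 10%, loss 20%, 78 and 94 per group. From section 2.1: 1:1 allocation. The article gives no absolute difference. Reading 10% as a tenth of the cohort mean (3.94 ml/kg/min, or 4.0 if rounded) is an assumption.

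**Step 1: reproduce 78.** The normal formula per arm is n = 2 (1.96 + 0.8416)² (SD / difference)².

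- Difference 4.0: 2 x 7.849 x (8.9 / 4.0)² = 77.7, so 78. This matches the article.
- Difference 3.94: 2 x 7.849 x (8.9 / 3.94)² = 80.1, so 81.

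So 78 reproduces as the number needed for analysis, with no loss allowance in it, when the difference is rounded to 4.0.

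**Step 2: reproduce 94.**

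- 78 x 1.2 = 93.6, so 94. This matches the article.
- 78 / (1 - 0.20) = 97.5, so 98 per arm, 196 in total.

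The stated target is therefore 4 per arm (8 in total) below what a 20% loss requires.

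**Step 3: what 94 per arm provides.**

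- Evaluable at 20% loss: 94 x 0.8 = 75.2, against the 78 required. For comparison, 98 x 0.8 = 78.4.
- Largest loss that still leaves 78: 1 - 78/94 = 0.170, or 17%.

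**Step 4: power cost of the inflation error alone.** Take the plan at its word that 78 evaluable per arm give exactly 80% power. Power at 75.2 per arm is then Φ(2.8016 x √(75.2/78) - 1.96) = Φ(2.751 - 1.96) = Φ(0.791) = 78.5%. A t-test calculation gives 78.5% as well. The cost is about 1.5 percentage points.

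**Step 5: the same with explicit inputs.** With a difference of 4.0, SD 8.9 and 75 per arm, power is 78.6% by the normal formula and 78.1% by the t test, so about 78%.

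**The case against.** The strongest reply is that very little follows from this. The shortfall is 4 patients per arm, and the inflation error alone costs about 1.5 points of power. The text calls the 20% loss only potential, and 94 per arm still covers losses up to 17%. The doubled clause looks like a drafting slip. All of this stands, and it limits the severity. It does not remove the contradiction or make 94 the right number for a 20% loss.

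Three stronger readings are tempting, and the article does not support them.

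- **That 78 already includes the loss.** A reader might infer about 62 evaluable per arm (78 x 0.8 = 62.4) and power of only 69 to 71%. The following sentence moves from 78 to 94 on account of the loss, the opening sentence fixes 94 per arm, and 78 reproduces in Step 1 without any loss. So 78 is the number before the allowance.
- **That power at 20% loss is 76.8%.** That figure (t test, 75 per arm) uses a difference of exactly 3.94. It mixes the inflation error with a separate rounding question: the article states no absolute difference, and 4.0 reproduces 78.
- **That the trial will in fact miss 80% power.** The SD of 8.9 is a cross-sectional value in ml/kg/min, whereas the primary outcome is the change in percent predicted VO2max, whose SD the article does not give. As an illustration, assume that the SD of change is 8.9 x √(2(1 - r)), where r is the correlation between baseline and month 12, and take a difference of 3.94. With 75 per arm, t-test power is about 69% at r = 0.4, 77% at 0.5, 81% at 0.55 and 85% at 0.6. True power could fall on either side of 80%.

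**Conclusion.** The point holds as an error of arithmetic and wording, of minor severity. The duplicated allowance and the 94-versus-98 discrepancy follow from section 2.6 alone and need no assumption about effect size or SD. On the plan's own terms, 20% loss leaves about 75 evaluable per arm instead of 78, and 188 patients are enough only up to about 17% loss.

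The statement about power is conditional: if 78 evaluable give 80%, about 75 give about 78.5%. It says nothing about the power that the trial will actually have, which depends on the unstated variability of the change in percent predicted VO2max.

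**What to change.** Reword one paragraph in section 2.6:

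1. Delete the 20% clause from the sentence that gives 78, so that 78 is plainly the number needed for analysis.
2. State the absolute difference and the SD used. The figure 78 reproduces with 4.0 and 8.9 ml/kg/min by the normal formula; a difference of exactly 3.94 gives 81.
3. Restate what 94 per arm achieves: either that it keeps 78 evaluable with up to about 17% loss, or that with 20% loss about 75 per arm are evaluable and power is about 78% for a difference of 4.0 and SD 8.9.

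No extra enrolment is needed for this. If the sponsor prefers to keep the claim of 80% power at 20% loss, the matching target is 98 per arm, 8 more patients in total. Otherwise the only cost is a slightly less favourable stated figure.
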